#### Intervention wards

In addition to the standard routine cataract screening services, there will be implementation of the co-developed intervention package, which will continue for two years. Screening camps will be done once per year for each cluster. Wards used for co-creation will also be included as part of intervention wards.

#### Control wards

Control wards will receive the standard community eye screening routine package as it has been carried out, at a frequency of once per year. A comparison of the two arms is shown in Table 1.

**Table 1. bpae016-T1:** Comparison of the two arms of the study.

Item	Intervention arm	Control arm
Community sensitization	Yes	
	Local announcements method available: posters and announcement in churches, mosques, and schools.	
	*Additional community-determined sensitization methods*	N/A
Provision of eye diseases screening camp at a ward	A team composed of ophthalmologist/cataract surgeon, two ophthalmic nurses, optometrist, and outreach coordinator	
	*Intervention facilitator for continued intervention implementation*	NA
Referral from ward to base hospital for surgery	Yes, with the standard usual support	
	*Additional community-determined support to attend base hospital*	NA
Assessment of primary outcome	Same for both arms (trained field worker)	
Assessment of referrals	Outreach team	
	*Study coordinators follow up for non-attenders*	
Post-op care	Standard care as usual	
	*Qualitative study on reason for non-attendance*	NA

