## Abstract

Age-related lens opacification (cataract) remains the leading cause of visual impairment and blindness worldwide. In low- and middle-income countries, utilization of cataract surgical services is often limited despite community-based outreach programmes. Community-led research, whereby researchers and community members collaboratively co-design intervention is an approach that ensures the interventions are locally relevant and that their implementation is feasible and socially accepted in the targeted contexts. Community-led interventions have the potential to increase cataract surgery uptake if done appropriately.

In this study, once the intervention is co-designed it will be implemented through a cluster-randomized controlled trial (cRCT) with ward as a unit of randomization.

This study will utilise both the qualitative methods for co-designing the intervention and the quantitative methods for effective assessment of the developed community-led intervention through a cRCT in 80 rural wards of Dodoma region, Tanzania (40 Intervention). The ‘intervention package’ will be developed through participatory community meetings and ongoing evaluation and modification of the intervention based on its impact on service utilization. Leask’s four stages of intervention co-creation will guide the development within Rifkin’s CHOICE framework. The primary outcomes are two: the number of patients attending eye disease screening camps, and the number of patients accepting cataract surgery. NVivo version 12 will be used for qualitative data analysis and Stata version 12 for quantitative data. Independent and paired t-tests will be performed to make comparisons between and within groups. P-values less than 0.05 will be considered statistically significant.

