### Study component II: Effectiveness of the intervention implementation

#### Study design and target population

The second study component will be a two-armed, pragmatic, cRCT to estimate the effectiveness of the community-developed intervention implementation. The clusters in this case are administrative rural wards of Dodoma region. The study will be pragmatic in the sense participants and data collectors will not be masked to the allocation status of the ward, and no attempts will be made to prevent ‘contamination’ of control wards by research activities conducted in intervention wards, thereby allowing estimation of a more ‘real-world’ effectiveness of the intervention [33].

The primary focus of this portion of the study is the effectiveness of the community-led interventions in increasing uptake of eye health screening services and cataract surgery. Figure 2 explains the study flow for schedule of enrolment, interventions, and assessment.

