## Study masking

Community-led interventions are difficult to blind since the wards are already classified into controls and intervention. However, the study statistician and the data clerks at the base hospital will be masked as to whether the patient comes from an intervention or control ward.

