## Data collection tools

All clinical data collected at screening camps will be captured in a standardized fashion, in real time using portable electronic devices running the CTO Survey data collection mobile app. The data will be backed up to a central, secure database at the end of each day. The database will be used to track individuals from study villages who were referred for cataract surgery and progression of implementation.

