## Description of variables

### Outcomes variables

#### Primary outcome

The primary outcome will be the proportion of all eligible persons with operable cataract who accepted and show up for cataract surgery at the base hospital overall and stratified by age, sex, and VA levels. Based on the 2022 population census, the appropriate population of people aged 50 years and above will be sought from the ward authorities for denominator calculation.

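### Table 1 gives assessment of the primary outcome to a trained field worker, so surgical attendance is not tied to the hospital staff whom the plan masks

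*Protocol article*

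**What the plan says.** Four places in the protocol article bear on who records the primary outcome and who is masked.

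- **Table 1 (under Control wards)**, row on assessment of the primary outcome: "Same for both arms (trained field worker"). A separate row gives assessment of referrals to the outreach team.
- **Study design and target population (component II)**: "participants and data collectors will not be masked to the allocation status of the ward". This is declared as part of the pragmatic design.
- **Study masking**: after conceding that blinding is difficult, it says that "the study statistician and the data clerks at the base hospital will be masked" to the arm of each patient's ward. No other role is named as masked.
- **Primary outcome**: the people counted are those who "accepted and show up for cataract surgery at the base hospital".

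Two further statements matter for the reading. The Abstract lists two primary outcomes, "the number of patients attending eye disease screening camps, and the number of patients accepting cataract surgery". Data collection tools says of the system that holds the camp data: "The database will be used to track individuals from study villages who were referred for cataract surgery". It does not say who enters the fact that a patient arrived for surgery.

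**The concern.** The event that defines the primary outcome takes place at the base hospital, where the plan has masked staff. Table 1 nevertheless names a field worker as assessor, and that role is not among the masked ones.

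Arrival for surgery leaves little room for judgement, so misclassification is not the main worry. Completeness is. Intervention wards have a facilitator, additional support to reach the hospital, and eye champions who keep diaries. If a field worker who knows the allocation is the source of the numerator, surgery may be picked up more fully in those wards than in control wards. Masking the statistician cannot restore events that were never recorded.

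**Working it through.** **Setting the statements side by side.** The masking point has no figure of its own to recompute.

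1. Named assessor: a trained field worker in both arms (Table 1).
2. Masked roles: the statistician and the base-hospital data clerks (Study masking). The field worker is not on this list.
3. Data collectors are unmasked (Study design and target population). The article does not say this of the field worker by name, but reading a field worker as a data collector is reasonable.
4. Site of the event: the base hospital (Primary outcome).
5. What the clerks record: not stated. That they could record surgical attendance follows from where they work.
6. Which outcome the Table 1 row means: not stated. The Primary outcome section has one primary outcome, surgery. The Abstract has two, and a field worker is the natural recorder of camp attendance.

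If the row means surgery, the assessor lies outside the masked roles. If it means camp attendance only, Table 1 names no assessor for surgery. On either reading, surgical attendance is not tied to the masked staff.

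**The plan's own figures, to check the inputs used below.** The sample size section gives c = 1 + (1.96 + 0.84)² × [(λ0 + λ1)/y + k²(λ0² + λ1²)] / (λ0 − λ1)², with λ1 = 1.3 λ0 and k = 0.4. Control rates are 0.198 (screening) and 0.045 (surgery) per person-year.

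- y = 2840: 38.85 wards per arm for screening and 40.06 for surgery.
- y = 1420: 39.21 and 41.63.

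The stated 39 and 42 are reproduced to within two wards with y = 2840, and after rounding with y = 1420.

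**Illustration of differential completeness.** The capture fractions s0 (control) and s1 (intervention) are assumptions; the documents give none. Suppose there is no true effect, and take λ = 0.045, k = 0.4, y = 2840 and c = 40 wards per arm.

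- Observed rates: l0 = 0.045 s0 and l1 = 0.045 s1. False rate ratio = s1/s0.
- SE = √{[(l0 + l1)/y + k²(l0² + l1²)]/(c − 1)} and d = (l1 − l0)/SE.
- Chance of a significant result = Φ(d − 1.96) + Φ(−d − 1.96).

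For 90% against 100%: l0 = 0.0405, l1 = 0.0450, SE ≈ 0.00398, d ≈ 1.13, chance ≈ 0.205.

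| Capture, control vs intervention (assumed) | False rate ratio | Chance of a significant result under no effect |
|---|---|---|
| 95% vs 95% | 1.00 | 0.050 |
| 95% vs 98% | 1.03 | 0.063 |
| 90% vs 95% | 1.06 | 0.090 |
| 90% vs 100% | 1.11 | 0.205 |

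As a share of the 30% target increase, 95% vs 98% is 0.032/0.30, about 11%, and 90% vs 100% is 0.111/0.30, about 37%. Equal under-recording in both arms produces no false ratio, so only a difference between arms matters.

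**The case against.** The case on the other side is substantial.

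- **A reader might infer that masked clerks already record the same event and that the plan passes over their record.** The article does not say what the clerks record. This stands; the point is only that they could do so.
- **A reader might see a contradiction between the design section and Study masking.** There is none. The first openly declares unmasked participants and data collectors; the second names the roles that can still be masked. Neither claims that masking protects ascertainment of the outcome.
- **The Table 1 row may refer to camp attendance**, with the hospital handling surgery. The Abstract makes this possible. It would remove the mismatch between Table 1 and Study masking, but the source for surgery would then be unnamed in that row.
- **There are safeguards.** The assessor type is the same in both arms, camp data are captured in a standard way, and the statistician is masked. The entry "Study coordinators follow up for non-attenders" may apply to both arms, but the table as extracted does not settle this. These limit the risk without tying surgery to a masked record.
- **A reader might conclude that the primary outcome is unprotected, or that a bias of 1.11 is to be expected.** Neither is supported. The event is fairly objective, nothing says that the field worker searches for or confirms surgery, and every capture fraction above is assumed.
- **An article may leave data sources to the full protocol.** That would excuse silence. Here Table 1 makes an explicit assignment, and it does not fit the stated masking.

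**Conclusion.** The point holds in a limited form and should be corrected. Table 1 names an assessor of the primary outcome who is outside the masked roles, while the outcome defined in the Primary outcome section occurs where masked staff work. This rests on two readings: that the field worker counts among the unmasked data collectors, and that the row covers surgical attendance at least in part.

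The risk is confined to differential completeness of recording. Its size cannot be derived from the documents. Under the assumed captures it runs from a false ratio of about 1.03 (95% vs 98%) to about 1.11 (90% vs 100%), and it is nil if capture is equal. The documents do not show that such a difference will occur.

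**What to change.** Split the Table 1 row in two.

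1. Camp attendance: recorded by the trained field worker in both arms.
2. Surgical attendance: taken from the base-hospital surgical register in both arms and entered by the masked data clerks. State the same source in Study masking and Primary outcome.

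Assign ward and arm afterwards by linkage. Use a referral number that reveals neither ward nor arm where the patient has one, and the recorded address otherwise. Linking by referral number alone would lose people who arrive without a camp referral. The Primary outcome section draws its denominator from the ward population aged 50 and over, and the sample size uses population rates, so those people should still be counted. The allocation list should stay away from the clerks, so that an address does not tell them the arm.

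The cost is wording, a neutral number on the written referral that is already issued, and a small amount of linkage work for patients without one. This assumes that the hospital register holds an address, which the article does not state. The intervention itself is unchanged.

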### Eligibility and recruitment

#### Clusters/wards/individuals

All rural wards of Dodoma region are eligible to be selected. A total of 80 wards will be selected at random from the administrative list of all wards and randomized 1:1 to control and intervention arms. All adults 50 years of age or older who attend community eye outreach camps will be enrolled.

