## Methods and analysis

### Study area

The study will be conducted in Dodoma region of Tanzania. Dodoma is administratively divided into eight district councils. Currently, there are a total of 3.08 million people, 209 wards and people aged 50 years and above account for approximately 10% of the population [27]. Dodoma is one of the regions with the highest prevalence of cataract blindness at 17.7%, which is above the national average of 15% [28]. To address eye health care needs, the regional eye care team has established a regular eye outreach programme since 2017. This justify and favours the settings of this trial to be done in Dodoma region, as there is ongoing community eye outreach programmes (CEOP) aiming at screening patients at their communities. These were initiated by the regional health committee and they have not shown to be very promising in increasing cataract services uptake and henceforth this community-led trial is designed. The current CEOP is done twice each month by a team of assistant ophthalmic medical officers, optometrist, ophthalmic nursing officer, and a Programme coordinator. The main activities entail screening for refractive errors and simple eye diseases by use of a pen torch. Those needing further management and/or surgery are listed down and referred to a base hospital.

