### Study population and follow-up

Using data from the 2022 Tanzanian national census (accounting for predicted annual population growth of 2.7% up to the year 2023 for Dodoma region), we expect an average of 1420 adults aged 50 years and above in each study arm (coefficient of variation = 0.4).

Two years of follow-up will yield a mean of 2840 person-years of observation per intervention arm. Based on unpublished findings from a pilot study involving four wards conducted in 2020 by our research team we anticipate a screening rate (i.e. rate of presentation to screening camps among population >50 years of age) of 0.198 per person-year in control villages with an inter-village coefficient of variation (k) of 0.4. For cataract surgery, we anticipate a rate of 0.045 per person-year in control villages based on an estimated prevalence of visually significant cataract of 17.7%, and cataract surgical coverage of 25%. We conservatively assumed we would observe a level of inter-ward variation in surgery acceptance rates like that for screening rates (k = 0.4).

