### Sample size, randomization, and allocation concealment

Using the sample size calculation method for unmatched cRCTs described by Hayes and Bennett [34], it is calculated that 40 wards will need to be enrolled in each study arm to achieve 80% power to detect a minimum 30% increase in screening examination and cataract surgery acceptance rates associated with the intervention at the 95% confidence level.

Population data from the 2022 Tanzanian national census (accounting for predicted population growth up to 2023) will be used, we expect an average of 1420 adults aged over 50 years in each study ward (coefficient of variation = 0.43).

The sample size calculation method for unmatched cluster-randomized trials with rate outcomes described by Hayes and Bennett was used:
c=1+Zα/2+Zβ2λ0+λ1y+k2λ02+λ12/λ0-λ12where c is the number of clusters, $Z_{\alpha /2}$ is the standard normal distribution based on level of significance (1.96), $Z_{\beta }$ is the standard normal distribution value based on the power of $100\left(1-\beta \right)\%$ (using 80% power $Z_{\beta }=0.84)$, $\lambda_{0\;}$ and $\lambda_{1}$ rates of the outcome in absence and presence of intervention, respectively, y is the person-years of follow-up in each group ward, and k = 0.4 is the coefficient of variation of the population rates between wards within each group. To detect a minimum 30% difference in outcome rates comparing intervention to control wards, we calculate that we will need to enrol 39 wards in each study arm for the presentation at screening camps outcome (outcome 1), and 42 wards in each arm for the cataract surgery outcome (outcome 2). To sufficiently power the study for both outcomes, we will sample a total of 40 wards in each study arm taking into account the design effect as well.

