#### Secondary outcomes

Proportion of all eligible persons attending at outreach eye examinations sites overall and stratified by age, sex, and VA levels (Screening rates)Acceptability, appropriateness, and fidelity of the community-led intervention. At study outset, distance of each study ward from the base hospital will be measured. Social economic status of each ward, Education levels, and economic activities of each ward will be obtained from the recent released National censors results.
*Acceptability* of the intervention will be assessed by using the standardized Acceptability of Intervention Measure questionnaires to evaluate the affective attitude, burden, perceived effectiveness, and ethicality of an intervention [35, 36].
*Appropriateness* will be assessed by using the Intervention Appropriateness Measure questionnaires to measure the perceived need, suitability, alignment, or compatibility of the intervention with the context, culture, or priorities of the participants and the research team [36].
*Fidelity* which is the extent to which the intervention is delivered or implemented as intended by community will be assessed using the Fidelity of Implementation Rating System checklist that evaluates the adherence, quality, and differentiation of an intervention delivery [37, 38].

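### Distance to the base hospital and district council have no stated role in allocation or the primary comparison, which may forgo precision in a trial with no spare power

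*Protocol article*

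**What the plan says.** **Allocation.** Under Clusters/wards/individuals the article states: "A total of 80 wards will be selected at random from the administrative list of all wards and randomized 1:1 to control and intervention arms". The section Sample size, randomization, and allocation concealment adds no stratum, match or constraint, and sizes the trial by the "sample size calculation method for unmatched cRCTs".

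**Ward-level data at hand.** Study area: "Dodoma is administratively divided into eight district councils". Secondary outcomes: "At study outset, distance of each study ward from the base hospital will be measured". That section also takes ward socio-economic status, education and economic activity from the census. The Introduction lists poor geographical access among the known barriers to cataract surgery.

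**Analysis.** Statistical analysis and data management compares arms by t-test or Wilcoxon test and models surgery acceptance with mixed effects to allow for clustering by ward. Baseline characteristics at participant and cluster level are adjusted for only in sensitivity analyses, and only where imbalances are found.

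**The concern.** The main outcome is turning up for surgery at the base hospital, so a ward's distance from that hospital bears directly on it. The trial plans to record distance before the intervention starts, yet the article gives it no role in allocation or in the main between-arm comparison. Its only route into the results is an adjustment that depends on what imbalance is seen and sits outside that comparison.

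Precision is at stake. In a trial of 80 large wards, the spread of true rates between wards sets the standard error, and more person-years per ward barely help. Explaining part of that spread with ward covariates is the main way to gain power without adding wards. The trial has little to spare, since it enrols fewer wards than its own calculation gives for the surgery outcome.

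**Working it through.** **Inputs from the article.** Control screening rate and between-ward variation: "of 0.198 per person-year in control villages with an inter-village coefficient of variation (k) of 0.4". Control surgery rate: 0.045 per person-year, with the same k. Target: "to achieve 80% power to detect a minimum 30% increase in screening examination and cataract surgery acceptance rates". Two-sided 5% level (z = 1.96), 80% power (z = 0.84), 40 wards per arm enrolled. Adults aged 50 and over per ward: 1420, so y = 1420 person-years over one year or 2840 over two. (The article attaches 2840 to an arm; it fits the formula only as a figure per ward.)

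**Formula.** c = 1 + (1.96 + 0.84)² × [(λ0 + λ1)/y + k²(λ0² + λ1²)] / (λ0 − λ1)², with λ1 = 1.3 λ0 and (1.96 + 0.84)² = 7.84.

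**Step 1: reproduce the article's ward numbers (k = 0.4).**

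| Outcome | y | (λ0+λ1)/y | k²(λ0²+λ1²) | (λ0−λ1)² | c |
|---|---|---|---|---|---|
| Screening | 1420 | 0.000321 | 0.016873 | 0.003528 | 39.2 |
| Surgery | 1420 | 0.0000729 | 0.000872 | 0.00018225 | 41.6 |
| Screening | 2840 | 0.000160 | 0.016873 | 0.003528 | 38.8 |
| Surgery | 2840 | 0.0000364 | 0.000872 | 0.00018225 | 40.1 |

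The stated 39 and 42 are reproduced at y = 1420.

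**Step 2: share of the variance that lies between wards.** Divide the k² term by the sum of both terms.
- Screening: 98% at y = 1420, 99% at y = 2840.
- Surgery: 92% at y = 1420, 96% at y = 2840.

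**Step 3: power with 40 wards per arm.** Power = Φ(√[(40 − 1)(λ0 − λ1)² / sum of both terms] − 1.96).
- Screening: 81% at either y.
- Surgery: 78% at y = 1420, 80% at y = 2840.

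**Step 4: power if covariates explain part of the between-ward variance.** Replace k by k√(1 − R²), where R² is the share explained by distance and council. R² is assumed, because the article gives no value.

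| Assumed R² | k | Screening, y = 2840 | Surgery, y = 2840 | Surgery, y = 1420 |
|---|---|---|---|---|
| 0 | 0.400 | 81% | 80% | 78% |
| 0.1 | 0.379 | 85% | 84% | 82% |
| 0.2 | 0.358 | 89% | 88% | 86% |
| 0.3 | 0.335 | 92% | 91% | 90% |

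At y = 1420, R² = 0.05 already brings the surgery requirement from 41.6 to 39.7 wards per arm, below the 40 enrolled.

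**Step 5: price of the adjustment.** Eight councils cost 7 degrees of freedom and a linear distance term costs 1, leaving 70 of 78. With a noncentral t distribution, if the covariates explain nothing, surgery power at y = 2840 falls from 79.9% to 79.8%.

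**Step 6: how large chance imbalance would be without restriction.** The standardized difference in a ward-level covariate has standard deviation √(2/40) = 0.224. It exceeds 0.25 in absolute value with probability 26%, and 0.5 with probability 2.5%. If each council supplied 10 wards (an assumption), at least one of the eight would split 7:3 or worse with probability 93%, and 8:2 or worse with probability 50%.

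**The case against.** A reader might infer three stronger charges. The documents support none of them.

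**That the allocation is faulty or biased.** Unrestricted randomization of 80 wards is valid. Chance imbalance does not bias the comparison, and a ward-level analysis carries it in the standard error. The article also does not say that allocation is unrestricted. It is silent, is a condensed account, and offers the randomization process on request under Data Availability. The unmatched formula does not rule out strata; using it for a stratified trial would be conservative.

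**That imbalance on known drivers of uptake is likely.** For distance, a difference above 0.25 SD has only a 26% chance. The high probabilities for councils concern any one of eight, rest on an assumed 10 wards each, and do not show that uptake differs by council. No passage reports such a difference.

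**That power is being given away.** The gain depends on an R² that the article does not supply. Most of it would come from adjusting in the analysis, not from stratified allocation, so the table in Step 4 does not measure what stratification alone adds. Study masking speaks of wards as already classified, so a new allocation may no longer be possible.

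All of this stands. What it leaves untouched is that the article does specify how ward covariates are handled: by sensitivity analysis conditional on observed imbalance. That stated choice can be improved at almost no cost. A statistical analysis plan not shown here may already do so.

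**Conclusion.** The point holds as a recommendation about precision, not as a fault that threatens validity. The article describes no use of distance or council in allocation, and confines ward covariates to sensitivity analyses that depend on observed imbalance. Its own figures put 92% to 99% of the variance between wards and give 78% to 80% power for surgery with 40 wards per arm, against a calculated need of 42.

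If distance and council explained 10% of between-ward variance, power would rise by about 4 points, to 85% for screening and 84% for surgery at y = 2840 (82% for surgery at y = 1420). That percentage is an assumption, and the true gain could be near zero. The case for distance rests on the article's own account of barriers. The case for council is weaker: there are district eye care coordinators and district-level CHMT members, so council is a natural administrative stratum, but the article does not show it to affect uptake.

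**What to change.** **In any case.** Before outcome data are seen, prespecify distance to the base hospital and district council as fixed terms in the primary ward-level regression or mixed-effects model, whatever balance is observed. Keep the unadjusted comparison as the sensitivity analysis. State whether the allocation was restricted, and on what.

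**If wards have not yet been allocated.** Also stratify the 1:1 allocation by council, split by near and far distance where numbers allow, or constrain it on the same two variables. Keep those terms in the primary model.

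**Cost.** About 7 to 8 of 78 degrees of freedom, or roughly 0.1 point of power if the covariates explain nothing. No extra wards and no new measurements are needed. If strata are used, the distance data must be compiled before the allocation instead of at study outset. If allocation is already made, the change is one sentence in the analysis section.
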